### Implementation Components and Procedures

#### Registry Component

The digital registry will be developed using the REDCap platform, a system widely used in clinical research for secure data collection, management, and analysis. The registry will be configured with role-based access, audit trails, structured data entry fields, mandatory and optional variables, and data quality checks. Access will be restricted to authorized project personnel, and all data management procedures will comply with applicable institutional policies and data protection regulations.

The registry will collect only anonymized or non–directly identifiable information required for research and service evaluation. Data fields will include child age group and sex, date and setting of contact, type of suspected maltreatment (physical, psychological, or sexual maltreatment; neglect; or exposure to domestic violence), warning signs, risk and protective factors, reporting source, referral or follow-up arrangements, and case management outcome. Each record will be assigned a unique alphanumeric study code. Direct identifiers, such as name, fiscal code, address, telephone number, or full date of birth, will not be entered into the research registry. Potential duplicate reports will be managed through predefined nonidentifying linkage variables, including time window, age group, sex, setting, and event characteristics, without attempting to reidentify the child.

Registry usability will be evaluated using the System Usability Scale (SUS), a validated 10-item questionnaire yielding scores from 0 to 100 [44]. SUS completion will be restricted to trained and authorized professionals with documented exposure to the registry, as detailed in the Outcomes and Measurement Time Points section. Feasibility indicators will include number of active users, number of records created, proportion of completed mandatory fields, average time required to complete a report, number of technical support requests, proportion of records with documented pathway activation, and completeness of follow-up fields. These indicators will allow for evaluation of whether the registry reduces data fragmentation and supports standardized clinical and operational terminology.

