The impact of the integrated registry training system on suspected maltreatment reporting will be assessed by comparing pre- and postimplementation reporting rates. The numerator will be the number of suspected maltreatment reports recorded during each observation period. The denominator will be the number of participating professionals and, when available, the number of pediatric consultations or service contacts during the same period. Reporting rates will therefore be expressed as reports per professional month and, where denominators are available, reports per 1000 pediatric contacts.

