### Outcomes and Measurement Time Points

The primary outcome is registry usability, measured using the mean SUS score collected after participants use the registry. Specifically, the SUS will be administered once at the end of the 12-month registry activation and follow-up period or earlier for participants who discontinue participation after having completed the minimum required registry exposure. Eligible respondents will be trained and authorized hospital or community professionals involved in suspected maltreatment recognition, documentation, or case management. To ensure that SUS responses reflect actual exposure to the tool, participants will be included in the primary SUS analysis only if they have entered at least one registry record or completed at least one supervised registry use session or simulation. Participants without any registry exposure will not contribute to the primary SUS analysis.

Secondary outcomes include feasibility indicators (active users, number of records, completion of mandatory fields, technical support requests, and time to complete a report), training outcomes (pretest-posttest knowledge and competency scores, satisfaction, and qualitative feedback), and reporting outcomes (number and rate of suspected maltreatment reports, reporting timeliness, duplicate reports, follow-up documentation, and activation of child protection pathways). Baseline data will be collected before training and registry activation, posttraining outcomes will be collected immediately after training, and registry usability and implementation outcomes will be collected during registry use and at the end of the observation period.

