### Data Management, Confidentiality, and Registry Workflow

Registry data will be entered using predefined forms by trained and authorized professionals. Records will be entered by the professional who identifies or manages the suspected case or by another authorized member of the clinical team directly involved in the case according to local organizational arrangements. Follow-up information will be updated when new nonidentifying information becomes available regarding referral, pathway activation, multidisciplinary evaluation, or case management outcome. Records will be saved under a unique study code and stored on secure institutional servers or approved REDCap infrastructure. The registry will not contain direct identifiers. Data access will be role based and limited to authorized members of the research team. Data exports for analysis will be anonymized, stored in password-protected files, and used only for the objectives approved by the ethics committee. Data quality will be checked periodically by designated members of the research team through REDCap validation rules, completeness checks, audit trails, and review of mandatory fields. Any inconsistencies, missing mandatory information, or potential duplicate records will be resolved using only nonidentifying registry information. Potential duplicate reports will be assessed through predefined nonidentifying linkage variables, including time window, age group, sex, setting, and event characteristics. When a potential duplicate is detected, the research team will retain a single registry record for analysis and update it with additional nonidentifying information when appropriate. Duplicate management will not involve access to direct identifiers and will not interfere with clinical or legal reporting procedures.

Any suspected maltreatment identified in clinical practice will continue to be managed through ordinary institutional and legal reporting pathways; the registry is an evaluation and documentation tool and does not replace mandatory reporting procedures. Mandatory reporting will remain a separate clinical and legal process carried out through existing institutional channels and according to applicable law. Entry of information into the research registry will be separate from the activation of the appropriate clinical and legal pathway and will not be considered a substitute for mandatory reporting. No direct identifiers or legal reporting documents will be uploaded to the registry.

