### Statistical Analysis

#### Overview

Quantitative analyses will be performed using recognized statistical software, such as SPSS, R, or Stata. Descriptive statistics will be calculated for all study variables. Continuous variables will be summarized as means and SDs or medians and IQRs according to distribution. Categorical variables will be summarized as frequencies and percentages. All estimates will be reported with 95% CIs when appropriate.

Pretest-posttest comparisons of knowledge and competency scores will be performed using 2-tailed paired-sample *t* tests when normality assumptions are met, as assessed using the Shapiro-Wilk test and visual inspection of distributions. When assumptions are not met, Wilcoxon signed-rank tests will be used. Mean change scores, standardized effect sizes, and 95% CIs will be reported to support interpretation of training effectiveness.

Registry usability will be evaluated by calculating the mean SUS score and comparing it with established interpretive benchmarks, where scores of 70 or higher are considered acceptable and scores of 80 or higher indicate excellent usability [44]. A 1-sample *t* test or Wilcoxon signed-rank test will be used to compare observed SUS scores with the prespecified benchmark depending on distributional characteristics.

Changes in reporting rates of suspected child maltreatment before and after implementation will be analyzed using Poisson regression models, estimating incidence rate ratios with 95% CIs. The primary pretest-posttest comparison will use reports per professional month as the operational denominator. When service volume data are available, additional models will use the number of pediatric consultations or contacts as an offset to estimate reports per 1000 contacts. Overdispersion will be assessed by comparing the deviance and Pearson chi-square statistics with the df; if overdispersion is present, negative binomial regression or robust SEs will be applied. Repeated reports and potential duplicates will be described separately and, in sensitivity analyses, excluded or counted once per suspected case according to the predefined duplicate management rules.

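### The protocol gives two incompatible rules for counting potential duplicate reports in the main pre-post reporting-rate model, and one of them, as written, deduplicates only the post-implementation period

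*Protocol article*

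**What the plan says.** The numerator of the reporting rate is defined under Registry Component: "The numerator will be the number of suspected maltreatment reports recorded during each observation period". The text does not say whether that number is taken before or after duplicates are resolved.

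Two sections then deal with duplicates.

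- Data Management, Confidentiality, and Registry Workflow: once a potential duplicate is detected, "the research team will retain a single registry record for analysis and update it with additional nonidentifying information when appropriate". The same section confines the resolution of duplicates to non-identifying information held in the registry.
- Statistical Analysis, Overview: "Repeated reports and potential duplicates will be described separately and, in sensitivity analyses, excluded or counted once per suspected case", and this is to be done "according to the predefined duplicate management rules".

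The model concerned is the Poisson regression of reports before and after implementation, for which "The primary pretest-posttest comparison will use reports per professional month as the operational denominator". Under Outcomes and Measurement Time Points it is a secondary outcome, in a list that begins "reporting outcomes (number and rate of suspected maltreatment reports, reporting timeliness, duplicate reports". The primary outcome is the System Usability Scale score.

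On timing, Study Design and Outcomes and Measurement Time Points both place the collection of baseline reporting activity before registry data entry is activated.

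**The concern.** The first rule removes potential duplicates before any model is fitted. The second leaves them in the main model and deals with them only in sensitivity analyses. For potential duplicates, an analyst cannot follow both, and the numerator definition does not say which prevails.

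The first rule raises a further problem. It draws on registry information, and the registry does not exist during the baseline period. If that rule governs, the text provides for cleaning the post-implementation count and says nothing about cleaning the baseline count.

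The rate ratio is the protocol's measure of whether reporting changed. Duplicates are to be expected: a record may be entered by the professional who identified the case, the one managing it or another team member, across hospital and community services. The protocol itself lists duplicates among its outcomes and performance indicators. The choice of rule can therefore move the estimate, and the two rules can move it in opposite directions.

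**Working it through.** **Plan's own figure.** There is none to reproduce. The protocol gives no expected count, rate ratio or power for the reporting-rate comparison, and no expected share of duplicates.

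**The two rules side by side**

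| Question | Data management section | Statistical Analysis overview |
|---|---|---|
| Potential duplicates in the main analysis | Collapsed to one record | All counted (implied) |
| Counting once | Part of preparing the data | A sensitivity analysis |
| Periods reached | Registry records only, hence post period | Not stated |

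If the left column governs, no detected duplicates remain for the sensitivity analysis to collapse. If the right column governs, the single-record rule is not followed in the main model. Reading the overview as concerned only with genuine repeat reports does not remove the conflict, because its sentence names potential duplicates as well.

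**Effect on the incidence rate ratio (IRR)**

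Inputs, all assumptions: d_pre and d_post are the shares of raw reports that are extra copies in each period, with a range of 0 to 20% before and 10 to 30% after. Detection is taken as perfect. If U is the rate of unique cases, the raw rate is U/(1 − d).

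- Both periods merged: IRR = U_post/U_pre = IRR_true.
- All reports counted in both periods: IRR = IRR_true × (1 − d_pre)/(1 − d_post).
- Only the post period merged: IRR = U_post ÷ [U_pre/(1 − d_pre)] = IRR_true × (1 − d_pre).

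With d_pre = 0.10 and d_post = 0.20:

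| True IRR | All counted | Post period only merged | Both merged |
|---|---|---|---|
| 1.0 | 0.90/0.80 = 1.125 | 0.90 | 1.00 |
| 1.5 | 1.5 × 1.125 = 1.69 | 1.5 × 0.90 = 1.35 | 1.50 |

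Over the whole assumed range, with a true IRR of 1:

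- All counted: from 0.80/0.90 = 0.89 (20% before, 10% after) to 1.00/0.70 = 1.43 (none before, 30% after). With equal shares the factor is 1 and there is no bias.
- Post period only merged: from 0.80 (20% before) to 1.00 (none before). This bias is never upward.

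**The word excluded.** Take 100 post-period records containing 20 duplicate pairs. Dropping the extra copy of each pair leaves 80; dropping both copies leaves 60. Counting once also leaves 80. The sensitivity analysis is thus either one analysis under two names or two different analyses, depending on a reading that the text does not settle.

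**The case against.** The strongest reply is that one clarifying sentence would do and that little more follows. Much of it is fair.

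- **Baseline fields.** A reader might infer that baseline reports lack the fields needed for matching. No section says so. The source of the baseline reports is unnamed, and a condensed article may leave it to the full protocol. What stands is narrower: the rule as written works from registry information, and the registry starts after baseline.
- **Asymmetry.** A reader might take the main count to be both double-counted and one-sided. These are alternatives. One-sided cleaning affects the main count only if the data management rule governs; if the overview governs, duplicates stay in both periods and any one-sidedness moves to the sensitivity analysis.
- **Redundant sensitivity analysis.** It is not wholly redundant. Repeat reports on one case need not be duplicate records, so counting once per case could still change the total after merging. The conflict is confined to potential duplicates.
- **Size.** It is tempting to say that duplicates inflate the ratio by 1/(1 − d_post). That holds only with no baseline duplicates.
- **Loss of information.** Merging need not be irreversible: audit trails are planned, duplicates are to be described separately, and keeping one record for analysis does not mean destroying the other. It remains true that a retained and updated record no longer separates the two reports in the analysis data.
- **Weight.** The outcome is secondary and the results are presented as pilot estimates. That limits the severity but leaves the conflict in place.

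**Conclusion.** The point holds in this form: the data management section and the Statistical Analysis overview contradict each other on whether potential duplicates enter the main pre-post reporting-rate model, and the numerator definition does not settle it. If the data management rule governs, deduplication as written reaches only the post period.

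The size is conditional on duplicate shares that the protocol does not give. At 10% before and 20% after, the two rules put an unchanged true rate on opposite sides of 1 (1.125 and 0.90). Other shares give larger or smaller gaps, and counting all reports is unbiased when the shares are equal. These figures illustrate sensitivity; they are not corrected trial results. They also assume that every duplicate is detected and that no two different children are matched.

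The documents do not support concluding that baseline data cannot be deduplicated, or that the primary usability outcome is affected. The matter should be settled before analysis, which according to the Results section has not begun.

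**What to change.** 1. State one rule for the numerator of the main pre-post model. One count per suspected event is preferable, applied to both periods with the same matching fields, provided the baseline reports carry comparable information.
2. If they do not, use all reports in both periods as the main count and give the post-only deduplicated count as a sensitivity analysis. Say openly that the main estimate then assumes similar duplicate shares before and after.
3. Flag suspected duplicates and link them to an index record, so that both counts can be produced from the same data.
4. Put whichever count is not the main one in the sensitivity analysis, and say whether excluding a duplicate means dropping the extra copy or the whole set.
5. State the source of the baseline reports and which matching fields they hold, and make the data management section and the Statistical Analysis overview agree.

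The cost is some wording, one REDCap flag field and, where available, a few matching variables from the baseline reports. Data collection is already under way, so the flag should be added soon and records merged so far should be checked against the audit trail.

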### Statistical Analysis

#### Overview

Quantitative analyses will be performed using recognized statistical software, such as SPSS, R, or Stata. Descriptive statistics will be calculated for all study variables. Continuous variables will be summarized as means and SDs or medians and IQRs according to distribution. Categorical variables will be summarized as frequencies and percentages. All estimates will be reported with 95% CIs when appropriate.

Pretest-posttest comparisons of knowledge and competency scores will be performed using 2-tailed paired-sample *t* tests when normality assumptions are met, as assessed using the Shapiro-Wilk test and visual inspection of distributions. When assumptions are not met, Wilcoxon signed-rank tests will be used. Mean change scores, standardized effect sizes, and 95% CIs will be reported to support interpretation of training effectiveness.

Registry usability will be evaluated by calculating the mean SUS score and comparing it with established interpretive benchmarks, where scores of 70 or higher are considered acceptable and scores of 80 or higher indicate excellent usability [44]. A 1-sample *t* test or Wilcoxon signed-rank test will be used to compare observed SUS scores with the prespecified benchmark depending on distributional characteristics.

Changes in reporting rates of suspected child maltreatment before and after implementation will be analyzed using Poisson regression models, estimating incidence rate ratios with 95% CIs. The primary pretest-posttest comparison will use reports per professional month as the operational denominator. When service volume data are available, additional models will use the number of pediatric consultations or contacts as an offset to estimate reports per 1000 contacts. Overdispersion will be assessed by comparing the deviance and Pearson chi-square statistics with the df; if overdispersion is present, negative binomial regression or robust SEs will be applied. Repeated reports and potential duplicates will be described separately and, in sensitivity analyses, excluded or counted once per suspected case according to the predefined duplicate management rules.

Associations between participant characteristics and outcomes will be explored using multivariable linear, logistic, or count regression models according to the distribution and nature of the dependent variable. Candidate predictors will include professional role, years of experience, work setting, previous child protection training, participation in practical sessions, and frequency of registry use. All analyses will be 2 tailed, with a significance level set at *P*<.05.

Missing data will be described by variable and time point. Complete-case analysis will be used for the primary pilot analyses. If the proportion and pattern of missing data justify it, multiple imputation or sensitivity analyses will be performed. Qualitative responses will be analyzed thematically by grouping open-text answers into recurrent categories related to usability, workflow integration, training usefulness, barriers, and facilitators.

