#### Sample Size Calculation

The sample size was determined to ensure adequate statistical power for detecting meaningful effects in both the usability and training evaluations. Assuming a medium effect size (Cohen *d*=0.5) for the improvement in knowledge and competency scores between pre- and posttraining assessments, a paired-sample *t* test with an α level of .05 and power (1 – β) of 0.80 requires a minimum of 27 participants.

This estimate aligns with the planned recruitment target of 25 to 30 professionals, which is considered sufficient to assess feasibility, usability, and preliminary impact within this exploratory pilot phase. For the SUS usability analysis, a sample of 25 participants allows for the estimation of the mean score with a 95% CI width of ±5 points, which is consistent with published methodological recommendations for usability testing in health care settings. Because this is a monocentric pilot study, analyses will be interpreted primarily as estimates of feasibility and effect size for future multicenter studies rather than as definitive evidence of effectiveness.

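### The primary outcome is the mean SUS score, but the plan allows its benchmark test to become a signed-rank test, which does not test a mean and can favour the registry when scores are clearly left-skewed

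*Protocol article*

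**What the plan says.** Outcomes and Measurement Time Points fixes the target: "The primary outcome is registry usability, measured using the mean SUS score collected after participants use the registry". Statistical Analysis, Overview, repeats it: "Registry usability will be evaluated by calculating the mean SUS score and comparing it with established interpretive benchmarks", and gives the benchmarks: "scores of 70 or higher are considered acceptable and scores of 80 or higher indicate excellent usability". The next sentence names the test, a 1-sample t test or "Wilcoxon signed-rank test will be used to compare observed SUS scores with the prespecified benchmark depending on distributional characteristics". It does not say which of 70 and 80 is the benchmark meant, or what in the distribution decides between the tests. Shapiro-Wilk and visual inspection are named in the same section, but only for the training scores.

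Tests are two-sided at .05 ("All analyses will be 2 tailed, with a significance level set at" .05). Sample Size Calculation states that "a sample of 25 participants allows for the estimation of the mean score with a 95% CI width of ±5 points", without giving an SD, and says results will be read mainly as estimates. Registry Phase Results promises the SUS mean, SD, median, IQR, 95% CI and the shares below 70 and above 80.

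**The concern.** The outcome is a mean, but the permitted fallback does not test a mean. The 1-sample signed-rank test gets its null distribution by attaching random signs to the ranked distances from the benchmark, so its null hypothesis is symmetry about the benchmark. If scores are symmetric, pseudomedian and mean coincide and nothing is lost. If they are skewed, the two separate, and skewness is a main reason to switch.

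The direction matters. On a 0–100 scale, a satisfied majority with a few very dissatisfied users gives left skew and puts the pseudomedian above the mean. Ranking also shrinks the weight of the users for whom the registry failed. The error therefore favours the registry, on the only primary outcome. The paper could then print a P value for being above the benchmark beside a 95% CI for the mean that includes it, with no rule for which governs.

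**Working it through.** **1. The plan's own SUS figure.** Half-width = t(0.975, 24) × SD / √25. For ±5: SD = 5 × 5 / 2.064 = 12.1 (with z: 25 / 1.96 = 12.8). No SD is stated, so the figure cannot be confirmed. SD 10 gives ±4.1, SD 15 gives ±6.2. An SD of about 12 to 13 is what the plan implies.

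**2. How far the two targets separate.** Assume 15% of users score 30 points below the rest, with mean 70. The majority centres on 74.5 and the minority on 44.5: 0.85 × 74.5 + 0.15 × 44.5 = 70. The pseudomedian is the median of averages of two independent scores:

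- both from the majority: 0.85² = 0.7225, centred on 74.5
- one from each: 2 × 0.85 × 0.15 = 0.255, centred on 59.5
- both from the minority: 0.15² = 0.0225, centred on 44.5

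With a normal within-group SD of 7, each average has SD 7/√2 = 4.95, and the median of this mixture is about 72.0. With a within-group SD of 10 (7.07 for averages) it is about 71.3. The mean is 70 in both.

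**3. Total SD.** Total variance = within-group variance + p(1 − p) × gap². With p = 0.15 and gap 30, the second term is 0.1275 × 900 = 114.75.

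- Within-group SD 7: √(49 + 114.75) = 12.8
- Within-group SD 10: √(100 + 114.75) = 14.7
- Within-group SD 12: √(144 + 114.75) = 16.1

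**4. False results above 70.** Monte Carlo, n = 25, true mean 70, scores on the 2.5-point SUS grid, 3,000 to 4,000 trials per shape. Assumed rule: Shapiro-Wilk P < .05 leads to Wilcoxon, otherwise the t test. Nominal upper tail 2.5%. All shapes are assumptions.

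| Shape | Total SD | Switching rule | t test |
|---|---|---|---|
| Normal | 12 | 2.4–2.9% | 2.9% |
| 15% of users 20 lower, within-group SD 10 | 12.3 | 3.8% | 3.5% |
| 15% of users 30 lower, within-group SD 12 | 16.1 | 4.4% | 3.5% |
| 15% of users 30 lower, within-group SD 10 | 14.7 | 5.9% | 4.2% |
| 20% of users 25 lower, within-group SD 6 | 11.7 | 9.1% | 4.9% |
| 15% of users 30 lower, within-group SD 7 | 12.8 | 11–12% | 5–6% |
| 12% of users about 34 lower, within-group SD 6 | 12.6 | 22.6% | 7.1% |
| 15% of users 40 lower, within-group SD about 7 | 16 | 22–23% | 6–7% |

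The rates at n = 30 are similar where they were run: 12.7% in the sixth row and 24.2–24.3% in the last two. The second and seventh rows have nearly the same total SD but 3.8% and 22.6%, so the shape, not the spread alone, drives the result.

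**5. Disagreement with the CI.** The switching rule was significant above 70 while the t-based 95% CI included 70 in 6.1% of trials with 15% of users 30 lower and within-group SD 7. That fell to 1.6% at within-group SD 10 and 0.9% at 12, and reached about 16% in the extreme shapes.

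**6. Alternative.** A bootstrap-t interval for the mean gave an upper-tail error of about 2–4% in the shapes on which it was tried.

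**The case against.** The strongest reply is that the size rests on a shape no document supports. The larger figures need a majority that agrees within about 6 or 7 points and a minority far below it. Widen the majority to a within-group SD of 10 to 12 and most of the excess over the t test goes. That stands, and it limits the claim: a reader might infer that any dissatisfied minority produces a false success, and the table shows otherwise. It does not remove the point, since two tight shapes (11.7 and 12.8) have total SDs close to what the plan's ±5 implies.

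The documents also limit the harm. The mean, its CI, the median and the share below 70 will all be reported, results are read mainly as estimates, and no success decision hangs on the P value. In the re-computed scenarios the signed-rank test never declared a result above 70 when the sample mean was 70 or lower, so the false result concerns the true mean. These points lower the severity but leave the target and its test unmatched.

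The Shapiro-Wilk trigger for SUS is an assumption, and the exact trigger can properly be left to an analysis plan. The mismatch cannot, because the article itself states both the outcome and the test.

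A reader might also infer the same error in the training comparison, where "When assumptions are not met, Wilcoxon signed-rank tests will be used" while a mean change is reported. The documents do not support that. If training has no effect and pre and post scores are exchangeable, the differences are symmetric about zero and the signed-rank test is valid. There the estimate and the P value merely rest on different methods.

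**Conclusion.** The point holds for the SUS analysis: the stated fallback does not test the stated primary outcome. Under clear left skew the error runs in the registry's favour. With 25 users and a true mean of 70, the false rate in the upper tail is roughly 9–12% against 5% for the t test with a tight majority, about 23% against 7% in more extreme shapes, 4–6% against 3–4% with a wider majority, and not raised under normality.

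These figures rest on assumed distributions, an assumed Shapiro-Wilk trigger, and reading the benchmark as 70; the argument is the same at 80. The study is an estimation-focused pilot, so this is a change worth making rather than a fatal flaw. It does not extend to a claim that the training test is invalid.

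**What to change.** In Statistical Analysis, Overview, state that the primary SUS analysis is the mean with its 95% CI, compared with one named benchmark, whatever the distribution. Use the 1-sample t test or, if scores are skewed, a bootstrap-t interval for the mean. Report the Wilcoxon test only as a sensitivity analysis, labelled as addressing location or symmetry.

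This takes one or two sentences and no new data, and the article says analysis has not begun. The downside is small: under strong skew the t test is itself mildly liberal, about 4–7% in the upper tail against 2.5%. The bootstrap-t interval largely corrects that, though not necessarily to nominal in the most extreme shapes.
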